### Study design

2.1

This is a parallel, triple-arm, randomized, sham-controlled trial designed to evaluate the clinical efficacy of the QNT and elucidate its neuroplasticity mechanisms in PD. Eligible PD patients will be randomized into three groups (1:1:1): verum acupuncture, sham acupuncture, or wait-list control. The total observation period spans 9 weeks, including a 1-week baseline, a 4-week intervention, and a 4-week follow-up. Additionally, 20 age- and sex-matched healthy controls (HCs) will be recruited to provide normative reference data for baseline MRI comparisons. The HCs data will be used to establish PD-related brain alterations by comparing HCs vs. PD patients at baseline, thereby identifying disease-specific structural and functional abnormalities that may be modulated by QNT.

The protocol adheres to the Standard Protocol Items: recommendations for Intervention Trials (SPIRIT (14) (Supplementary material 1) and the Standards for Reporting Interventions in Clinical Trials of Acupuncture (STRICTA) (15). A flowchart of the study design is shown in Figure 1, and assessment time points are detailed in Table 1.

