### Sample size

2.3

This trial is designed as an exploratory mechanistic study, with the primary objective of detecting QNT-induced neuroplasticity using multimodal MRI. The sample size was therefore determined based on neuroimaging methodology standards. Given the lack of standardized methods for sample size estimation in acupuncture-related neuroimaging trials, we referenced fMRI studies that recommended ≥20 participants per group for robust statistical analysis (17). Accounting for a 10% attrition rate, 69 PD patients (23 per group) and 20 HCs will be enrolled. HCs undergo baseline MRI only, minimizing dropout risk. Separately, a formal power calculation for the UPDRS-III was performed using PASS 15.0. Based on our pilot data (7), the expected changes (mean ± SD) are: verum acupuncture group 14.0 ± 9.94, sham group 2.84 ± 3.08, and wait-list group 2.3 ± 3.0 (18). With α = 0.05, power = 0.90, 1:1:1 allocation, and Tukey–Kramer correction for multiple comparisons, the required sample size is 165 patients (55 per group) after adjusting for 20% dropout. This trial, however, is designed as an exploratory mechanistic study; the smaller sample of 69 patients is adequately powered for the primary neuroimaging endpoints, whereas all clinical efficacy analyses are considered exploratory and will inform the design of future large-scale multicenter trials.

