##### Unified Parkinson's Disease Rating Scale part III (UPDRS-III)

2.6.1.1

Although all clinical analyses are exploratory, the change in UPDRS-III total score from baseline to week 4 is designated as the primary clinical outcome measure to maintain temporal alignment with the primary neuroimaging assessments. The UPDRS, revised by the Movement Disorder Society (MDS) in 2008 (20), is the gold standard for comprehensive PD symptom assessment (21). The Chinese version of the PD scale has excellent reliability and validity in Chinese PD patients (22). The UPDRS-III evaluates motor function via 18 items scored from 0–4 (higher scores indicate greater impairment). Assessments will occur at baseline, week 4 (post-treatment), and week 8 (end of follow-up; Table 1).

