#### Clinical data analysis

2.9.1

All statistical tests will be two-tailed, with significance set at α = 0.05. Baseline demographic and clinical characteristics will be summarized descriptively by group. Baseline demographic and clinical characteristics will be summarized descriptively by group. To assess baseline comparability among the three randomized groups, one-way ANOVA (or Kruskal–Wallis test) will be used for continuous variables, and chi-square tests for categorical variables. If significant between-group differences are observed at baseline, the affected variables will be included as covariates in subsequent analyses to adjust for potential confounding. For the primary clinical outcome, no correction for multiple comparisons is applied as this is a single predefined comparison. For secondary clinical outcomes, we will apply False Discovery Rate (FDR) correction within each assessment scale. Continuous data will be analyzed via one-way ANOVA (normally distributed data) or the Kruskal–Wallis *H*-test (non-normal data), with Bonferroni-adjusted *post-hoc* comparisons. Categorical variables will be analyzed using the Pearson χ^2^ test or Fisher's exact test for unordered variables, and the linear trend χ^2^ test for ordered variables. Analysis of covariance (ANCOVA) will be employed to adjust for baseline values, age, disease duration, and levodopa equivalent daily dose where appropriate. If significant baseline differences between groups are observed after randomization, these variables will be included as covariates in the corresponding models to mitigate bias. Missing data will be handled using multiple imputation by chained equations under the missing at random assumption, with sensitivity analyses comparing imputed results to complete-case analyses. An intention-to-treat (ITT) analysis will include all randomized participants, whereas per-protocol analyses will exclude non-compliant cases (< 80% session attendance).

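### The primary clinical outcome is exempted from correction as one predefined comparison, but no pair of arms is named and the stated Bonferroni rule conflicts with the exemption

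*Protocol article*

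**What the plan says.** Section 2.1 of the Protocol article sets up three arms: "Eligible PD patients will be randomized into three groups (1:1:1): verum acupuncture, sham acupuncture, or wait-list control". Section 2.6.1.1 picks the leading clinical outcome: "the change in UPDRS-III total score from baseline to week 4 is designated as the primary clinical outcome measure". The opening clause of that sentence says that all clinical analyses are exploratory, as do sections 2.3 and 2.6.1.

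Section 2.9.1 sets the level: "All statistical tests will be two-tailed, with significance set at α = 0.05". It then exempts this outcome: "For the primary clinical outcome, no correction for multiple comparisons is applied as this is a single predefined comparison". Secondary clinical outcomes get FDR correction within each scale. The next sentence covers continuous data in general: "Continuous data will be analyzed via one-way ANOVA (normally distributed data", or Kruskal–Wallis for "non-normal data), with Bonferroni-adjusted" post-hoc comparisons. It makes no exception for UPDRS-III.

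Section 2.3 reports a separate UPDRS-III power calculation that uses "1:1:1 allocation, and Tukey–Kramer correction for multiple comparisons". That calculation gives 165 patients and does not set the trial's size, which rests on imaging practice: "Accounting for a 10% attrition rate, 69 PD patients (23 per group) and 20 HCs will be enrolled".

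**The concern.** One outcome in three arms is not by itself one comparison; there are three possible pairs. The exemption rests on a contrast having been fixed in advance, yet the text gives no arms for it. The reader cannot supply them safely. The Discussion gives both control arms an inferential role: sham to isolate the specific effect, wait-list to account for disease progression and non-specific effects.

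The exemption also sits two sentences before a Bonferroni rule that, read literally, covers the same variable. The power calculation for that variable assumes that all pairs are compared.

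Two things are at stake. First, the error rate attached to the result labelled as the primary clinical one is not fixed. Second, the choice of contrast could be made after the data are seen. Sections 2.4 and 3 concede that participants cannot be blinded between acupuncture and wait-list, so the contrast most open to bias could be reported as primary.

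**Working it through.** **Inputs.** Two-sided α = 0.05 (section 2.9.1); three arms, 1:1:1 (section 2.1); 23 randomized per arm (section 2.3), or about 20 evaluable, since 23 × 0.90 = 20.7. Assumptions: normal outcomes, equal SDs, all arms equal under the null. Error df with 23 per arm = 3 × 22 = 66.

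**1. The plan's own premise.** One named contrast at two-sided 0.05 has error 0.05 by construction. Simulation of 200,000 trials gave 0.0497. The omnibus F test alone also has 0.05 (simulated 0.0496). If there is one comparison, leaving it uncorrected is sound.

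**2. All three pairs, uncorrected and ungated.** The tests share arms, so the exact figure comes from the studentized range Q for 3 groups and 66 df:

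P(Q > √2 × t(0.975; 66)) = P(Q > √2 × 1.9966) = P(Q > 2.8236) = 0.121.

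Wrongly treating the tests as independent would give 1 − 0.95³ = 0.143.

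**3. Both verum contrasts, uncorrected.** Simulation gives 0.090.

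**4. Pairs tested only after a significant omnibus F.** Simulation gives 0.050. With three groups this gate holds the family-wise rate at 5%.

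**5. Bonferroni over three pairs.** Each test is at 0.05/3 = 0.0167, with critical t(66) = 2.4565. P(Q > √2 × 2.4565) = P(Q > 3.4741) = 0.043. Tukey gives 0.049.

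| Reading | Family-wise error |
|---|---|
| Bonferroni on all three pairs | 4.3% |
| Tukey on all three pairs | 4.9% |
| One contrast, omnibus alone, or pairs gated by the omnibus test | 5% |
| Both verum contrasts uncorrected | 9.0% |
| All three pairs uncorrected and ungated | 12.1% |

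At 20 per arm the results agree to within 0.002.

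**6. Power cost if Bonferroni governs verum versus sham.** Section 2.3 expects changes of 14.0 ± 9.94 and 2.84 ± 3.08, a difference of 11.16. The two-arm SD is √((9.94² + 3.08²)/2) = 7.36, so d = 11.16/7.36 = 1.52. With 20 per arm, t-test power is 99.7% at 0.05 and 98.7% at 0.0167. With SD 9.94 in both arms, d = 11.16/9.94 = 1.12 and power is 93% and 85%. The loss is about 1 to 9 percentage points.

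**The case against.** The strongest reply is that the plan never says that three uncorrected tests will be run. It says that there is one comparison, and it prescribes an omnibus test with post-hoc pairs after it. A reader might infer that the rule as written gives 12% error. It does not: that figure needs all three pairs, each at 0.05, with no gate, and several readings give 5% or less.

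It can also be said that there are not three rival analysis rules. Tukey–Kramer appears only as a planning assumption in a calculation that does not set the 69. The Bonferroni sentence follows the one on secondary outcomes and might be meant for those alone. The first point stands: Tukey–Kramer shows that the authors had several comparisons in mind, but it is not an analysis rule. The second stands only in part. On that reading secondary outcomes would carry both FDR and Bonferroni, and the primary clinical outcome would have no stated between-group test except ANCOVA where appropriate.

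A reader might further infer a heavy loss of power under Bonferroni. The protocol's own figures support only the small loss in step 6.

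Finally, the clinical outcomes are declared exploratory and the primary endpoint is imaging, so no confirmatory conclusion rests on this test. That stands and lowers the severity. It does not remove the contradiction, because the article still designates a primary clinical outcome, sets a significance level for it, and describes its comparison as predefined. Nor is this detail that an article may leave to a fuller plan: the stated reason for the exemption conflicts with the rest of the text.

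**Conclusion.** The point holds as an inconsistency of moderate severity. The exemption depends on a contrast that the article does not name, and it conflicts with the Bonferroni sentence in the same section as that sentence is written. The all-pairs assumption in section 2.3 also fits poorly with it. The documents support a range of about 4.3% to 12.1% for family-wise error, with 12.1% as the upper end and not the plan's stated rate.

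The figures assume equal SDs. The SDs in section 2.3 are very unequal; if they held under the null, a test using the variance pooled over all three arms would have about 10% error even for verum versus sham alone (simulation, 23 per arm). That is an assumption about the null, not a figure from the protocol, and the conclusion does not depend on it.

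**What to change.** 1. In sections 2.6.1.1 and 2.9.1, name verum versus sham, UPDRS-III change from baseline to week 4, two-sided 0.05, as the single primary clinical comparison. It is the contrast that tests the specific needling effect with participants blinded.
2. State that the omnibus test and the wait-list contrasts are supportive, under one stated correction. The existing Bonferroni rule is enough; a fixed sequence is an alternative, not a requirement for exploratory outcomes.
3. Exempt the primary contrast explicitly from the Bonferroni post-hoc sentence.
4. Restate the UPDRS-III calculation in section 2.3 for that contrast and α, in place of the Tukey–Kramer assumption.

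The cost is a few lines of text and one rerun calculation. The enrolled number does not change, because 69 does not come from that calculation. The small downside is that the wait-list contrasts become supportive only.

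### The analysis of continuous clinical outcomes shares one variance across arms although the plan expects a threefold difference in SD, so its confidence intervals misstate precision

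*Protocol article*

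**What the plan says.** Section 2.3 (Sample size) gives the expected UPDRS-III changes as mean ± SD: "verum acupuncture group 14.0 ± 9.94, sham group 2.84 ± 3.08, and wait-list group 2.3 ± 3.0". The wait-list figures carry a separate citation.

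Section 2.9.1 (Clinical data analysis) sets the tests. The level is fixed by "All statistical tests will be two-tailed, with significance set at α = 0.05". The main rule is "Continuous data will be analyzed via one-way ANOVA (normally distributed data", with Kruskal–Wallis when data are not normal and Bonferroni adjustment of the post-hoc comparisons. For adjustment it adds "Analysis of covariance (ANCOVA) will be employed to adjust for baseline values, age, disease duration, and levodopa equivalent daily dose where appropriate". The same section says the primary clinical outcome needs no multiplicity correction because it is one predefined comparison, but does not say which comparison that is.

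Normality is the only property of the data that changes the method. The article mentions no check of equal variances, Welch or Games–Howell procedure, robust standard error or arm-specific variance.

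Sections 2.3, 2.6.1 and 2.6.1.1 make the MRI biomarkers the primary endpoint and all clinical analyses exploratory. Section 2.6.1.1 still names UPDRS-III change from baseline to week 4 as the primary clinical outcome.

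**The concern.** In their standard form, one-way ANOVA and ANCOVA estimate one residual variance from all arms and use it for every pairwise contrast. Here two of the three arms are expected to vary little and one to vary a great deal. The shared variance is then too small for any contrast that includes verum and too large for the contrast that does not.

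The familiar reassurance that equal allocation protects the test applies to a two-arm pooled t-test. It does not carry over to a pairwise contrast whose error term also contains a third, low-variance arm.

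At stake are the intervals on the clinical results. Section 2.3 says these analyses will inform future larger trials, so an honest interval matters more than the p-value. The Discussion also relies on the wait-list arm to estimate non-specific effects of sham, and that interval is affected in the opposite direction.

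**Working it through.** **Inputs.** SDs 9.94, 3.08 and 3.0 and means 14.0, 2.84 and 2.3 (section 2.3); two-sided 5% (2.9.1); 23 per arm enrolled, about 20 evaluable after 10% attrition (2.3).

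**The plan's own sample sizes.** The enrolled number reproduces: 20/(1 − 0.10) = 22.2, rounded up to 23 per arm, 69 in all. The 165 quoted for UPDRS-III (55 per arm, or 55 × 0.8 = 44 evaluable) does not. With 90% power and a Tukey critical value, verum versus sham needs 10 per arm at a common SD of 6.25 and 22 at 9.94, which is 13 to 28 after 20% dropout. Nothing below depends on the 165.

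**Variance ratios.** Variances are 98.80, 9.49 and 9.00. Verum to sham is 98.80/9.49 = 10.4; verum to wait-list is 98.80/9.00 = 11.0.

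**Pooled SD with equal arms.** √[(98.80 + 9.49 + 9.00)/3] = √39.10 = 6.25.

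**Standard errors**, each to be divided by √n. Pooled, for any pair: √(2 × 39.10) = 8.84.

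| Contrast | True | Pooled | Pooled/true |
|---|---|---|---|
| Verum – sham | √(98.80 + 9.49) = 10.41 | 8.84 | 0.85 |
| Verum – wait-list | √(98.80 + 9.00) = 10.38 | 8.84 | 0.85 |
| Sham – wait-list | √(9.49 + 9.00) = 4.30 | 8.84 | 2.06 |

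**Large-sample error of verum – sham at nominal 5%.** 2 × [1 − Φ(1.96 × 0.85)] = 9.6%, so interval coverage is about 90.4%. The coverage result does not depend on the true means.

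**Simulation**, normal data with the stated SDs (100,000 runs; 20,000 for ANCOVA with four covariates):

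| Quantity | 20 per arm | 23 per arm |
|---|---|---|
| Coverage of nominal 95% interval, verum – sham | 90.0% | 90.0% |
| Verum – sham rejection at equal means, uncorrected 5% | 9.95% | 10.0% |
| Same, ANCOVA | 9.8% | 10.0% |
| Same, read only after a significant F | 6.9% | 6.8% |
| Same, Bonferroni level 1.67% | 4.55% | 4.5% |
| Any of three pairs, Bonferroni (familywise) | 6.2% | 6.2% |
| Overall F test | 7.6% | 7.5% |
| Two-arm pooled t-test, verum and sham only | 5.5% | 5.4% |
| Sham – wait-list, uncorrected 5% | 0.04% | 0.03% |

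Coverage is also 90.0% at the means in section 2.3. At 23 per arm the mean 95% half-width for verum – sham is 3.65 points pooled and 4.42 with Welch. For sham – wait-list it is 3.65 pooled and about 1.80 unpooled.

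**The Kruskal–Wallis branch.** With these SDs and equal means its overall test rejects about 6.4–6.7% of the time, so it does not remove the problem.

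**After the change.** Welch for verum – sham gives 5.0% at both sizes, and 1.6–1.7% at the 1.67% level. ANCOVA with HC3 gives 4.9% and 5.1%.

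**The case against.** **Section 2.9.1 does not commit to the worst case.** It lists an uncorrected single comparison, ANOVA, Bonferroni post-hoc tests and ANCOVA without saying how they combine for UPDRS-III. A reader might infer that the plan's clinical test simply runs at 10%. The document does not support that without conditions: 10% needs an uncorrected verum–sham contrast, not gated by the F test, on the three-arm variance. Other permitted readings give about 7%, 4.5% against a 1.67% level, or 5.4%. This stands.

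**The null scenario is an added assumption.** Section 2.3 attaches the SD of 9.94 to a mean change of 14.0. If the verum SD under no effect were 5, the large-sample figure would be about 7%; if 3, about 5%. This stands for the rejection rates but not for the coverage figure, which needs no null.

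**The normality switch may act.** Under the stated SDs, a Shapiro test on the combined residuals rejects in 83–88% of simulations, which would send the analysis to Kruskal–Wallis. Tested arm by arm, it does so in only about 14%. The section does not say which check is meant, so how often ANOVA would actually be used is uncertain.

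**Sham versus wait-list.** One might conclude that pooling makes this contrast untestable. The expected difference is only 2.84 − 2.3 = 0.54 points. Unpooled power is about 9% at 20 to 23 per arm, and 90% power would need at least 667 per arm. The contrast is weak because of its size; pooling only makes its interval needlessly wide.

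**Inputs and scope.** The SDs are for raw change; residual SDs after covariate adjustment are unknown. The outcomes are exploratory, and an analysis plan not shown here might name Welch or robust errors. Even so, the article names specific methods whose standard form conflicts with its own inputs, which goes beyond leaving out detail.

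**Conclusion.** The point holds as one about precision. If SDs near 9.94, 3.08 and 3.0 occur and contrasts use the shared three-arm variance, standard errors for both verum contrasts are about 15% too small (the true value is about 1.18 times the pooled one for verum – sham). Their nominal 95% intervals cover about 90%, and the sham – wait-list interval is about twice too wide.

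Error inflation is conditional on the SDs remaining unequal when the means are equal, and on which reading of section 2.9.1 is applied.

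Two stronger inferences are not supported. The verum–sham conclusion at the planned effect would not change: at the stated means Welch at the Bonferroni level still has 98.3% power at 20 per arm and 99.2% at 23. Nor does the calculation bear on the MRI primary endpoint, since it uses only the UPDRS-III SDs. The change is worth making because it is cheap and affects the named primary clinical outcome, but it does not threaten the trial's main objective.

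**What to change.** In section 2.9.1, state that variances will not be assumed equal across arms for UPDRS-III and the other continuous clinical outcomes:

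- without covariates, Welch ANOVA with Games–Howell pairwise comparisons in place of one-way ANOVA with pooled post-hoc tests;
- with covariates, ANCOVA with HC3 standard errors or arm-specific residual variances.

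Adopt this before database lock and without a preliminary test of equal variances, so that the method does not depend on the data.

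The cost is about one sentence and a software option. If the variances prove equal, the verum–sham half-width at 23 per arm rises from 3.67 to 3.70 points (3.70/3.67 = 1.008), about 1%.

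### No single analysis governs the UPDRS-III change: an undefined normality criterion chooses between ANOVA and Kruskal–Wallis, and neither suits the unequal SDs the plan expects

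*Protocol article*

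**What the plan says.** Section 2.9.1 (Clinical data analysis) sets the rule for continuous clinical outcomes: "Continuous data will be analyzed via one-way ANOVA (normally distributed data"), or Kruskal–Wallis when data are non-normal, with Bonferroni-adjusted pairwise comparisons afterwards. It gives no test of normality, no level, and no statement of what is checked: each arm, the residuals or the pooled values. The rule covers the UPDRS-III change from baseline to week 4, which section 2.6.1.1 makes the primary clinical outcome.

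The same paragraph says separately that ANCOVA will adjust for baseline value, age, disease duration and levodopa equivalent dose where this is suitable. It does not tie ANCOVA to either branch or say that it gives the main result. It also says "Missing data will be handled using multiple imputation by chained equations under the missing at random assumption".

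Section 2.3 (Sample size) gives the expected UPDRS-III changes: "verum acupuncture group 14.0 ± 9.94, sham group 2.84 ± 3.08, and wait-list group 2.3 ± 3.0". On numbers it says "Accounting for a 10% attrition rate, 69 PD patients (23 per group) and 20 HCs will be enrolled". Sections 2.3 and 2.6.1 declare all clinical analyses exploratory, and section 2.3 says they will inform the design of later multicentre trials.

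**The concern.** Three analyses are named for one outcome and none is designated. The choice between the first two depends on the outcome data, through a criterion that the analyst would have to supply.

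The branches answer different questions. ANOVA compares mean changes, the scale on which section 2.3 states its expectations. Kruskal–Wallis compares rank distributions. It yields a test statistic, not a difference in UPDRS-III points with a standard error, so it sits badly with multiple imputation and with the ANCOVA named in the same paragraph.

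A normality check also looks for the wrong problem. The expected SDs differ more than threefold between arms. Ordinary ANOVA assumes them equal, and nothing in section 2.9.1 addresses this.

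At stake is the effect estimate and interval that a later trial would be planned on.

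**Working it through.** **Inputs.** From section 2.3: mean changes 14.0, 2.84 and 2.3; SDs 9.94, 3.08 and 3.0; 23 per arm randomized and about 20 per arm after attrition. From section 2.9.1: two-sided α = 0.05. Assumed, because the plan does not say: normal data within each arm, and Shapiro–Wilk at 5%. The plan states no failure rate for its normality check, so there is no figure of its own to reproduce.

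**1. SD ratio.** 9.94/3.08 = 3.23 and 9.94/3.0 = 3.31.

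**2. How often the switch occurs.** Simulated, 2,000 to 6,000 trials per setting:

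| What is checked | 20 per arm | 23 per arm |
|---|---|---|
| Each arm (any arm fails) | 14% | 15% |
| ANOVA residuals | 83–84% | 88–89% |
| ANCOVA residuals (baseline SD 8 to 16 assumed) | 80–82% | 85–86% |
| Pooled raw changes | about 100% | about 100% |

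The per-arm figure is what chance predicts for three normal arms: 1 − 0.95³ = 14.3%. It rises to about 21–22% if changes are rounded to integers, and to 58% (20 per arm) or 65% (23 per arm) if verum changes follow a skewed gamma distribution (an assumption). For residuals, Lilliefors gives 66% and 71%, and a plain Kolmogorov–Smirnov test 7% and 10%.

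**3. Why the residuals fail.** Residuals have the arm means removed, so the treatment effect on the mean plays no part. What remains is a mixture of three normal distributions with different variances. Its kurtosis is 3 × mean(σ⁴) / (mean σ²)². The variances are 98.80, 9.49 and 9.00, with mean 117.29/3 = 39.10. The sum of their squares, which is three times their mean, is 9,933. Kurtosis = 9,933/39.10² = 6.5, against 3 for a normal distribution. When residuals are first divided by their arm's SD, the failure rate falls to about 4–5%. Pooled raw changes fail for both reasons: unequal SDs and unequal means.

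**4. Intervals under ordinary ANOVA** (20 per arm, pairwise comparisons using the pooled error).
- Pooled SD = √39.10 = 6.25, so the standard error of any difference is 6.25 × √(2/20) = 1.98, with t = 2.00 on 57 df.
- Verum versus sham: true SE = √((98.80 + 9.49)/20) = 2.33. The interval reaches 2.00 × 1.98/2.33 = 1.70 true SEs, for coverage of about 91%. Simulated: 90%.
- Sham versus wait-list: true SE = √((9.49 + 9.00)/20) = 0.96. The interval reaches 2.00 × 1.98/0.96 = 4.1 true SEs, for coverage of nearly 100%. Simulated: about 100%, with mean half-width 3.9 points against 1.9 for Welch.
- Welch intervals cover about 95% for both contrasts.

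**5. Rejection rates** (20 / 23 per arm):

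| Analysis | Equal means, planned SDs | Planned means and SDs |
|---|---|---|
| ANOVA | 7.2% / 7.4% | 99.9% / 100% |
| Kruskal–Wallis | 6.4% / 6.9% | 99.1% / 99.7% |
| Switch on residual check | 7.6% / 7.7% | 99.1% / 99.7% |
| Welch ANOVA | 4.9% / 5.6% | 99.2% / 99.7% |

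**The case against.** The strongest defence is that the clinical analyses are declared exploratory, the primary endpoint is MRI with its own analysis section, and both tests reject in at least 99% of trials under the planned means. That stands and limits the weight of the point. It does not remove it: the declared use of the clinical results is to plan later trials, and that needs an estimate and a valid interval more than a p-value.

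Several stronger readings are tempting, and the document does not support them.

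- *The main result will go to Kruskal–Wallis in most trials.* Section 2.3 gives means and SDs, not shapes, and section 2.9.1 does not say what is checked. A per-arm check fits the text equally well and, with normal arms, would usually pass.
- *The switch strips out baseline adjustment.* One-way ANOVA takes no covariate either, and the ANCOVA sentence is not conditional on normality. The fault is that no governing analysis is named.
- *The switch costs much power.* With the plan's own figures it costs almost none.
- *Multiple imputation becomes impossible, or later trials would get only a p-value.* The plan names no pooling rule, and approximations exist for combining chi-square statistics. Means and SDs can also be reported beside a rank test. What the rank branch lacks is an adjusted mean difference with a standard error to pool.

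A separate analysis plan could name the check. The choice would still depend on the outcome data, and the check would still not address unequal variances.

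**Conclusion.** The point holds as one about estimation and pre-specification. Section 2.9.1 fixes no governing analysis for the UPDRS-III change and leaves the choice of test to an undefined criterion. With Shapiro–Wilk, the rate of switching runs from about 14% to nearly 100% according to what is checked; a plain Kolmogorov–Smirnov test on residuals would put the lower end at 7–10%. Neither branch suits the expected data. The rank branch supplies no adjusted mean difference, and the ANOVA branch supplies intervals that are too narrow for verum versus sham (about 90% coverage) and about twice as wide as needed for sham versus wait-list. Under equal means with these SDs, type I error is about 6–7% for either test alone and nearly 8% for the two combined by a residual check.

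These sizes rest on the SDs in section 2.3, normal data within arms, and pairwise comparisons that use the pooled ANOVA error. If the observed SDs were similar across arms, the coverage and type I error problems would largely go, but the undesignated analysis would remain. The change should be made; the exploratory status of the clinical outcomes keeps it from being critical.

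**What to change.** In section 2.9.1, delete the normality-based choice and name one analysis for every continuous clinical outcome:

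- a linear model of the week-4 value (or the change, which gives the same arm contrasts once baseline is in the model) on arm and baseline value, with any further covariates from the existing ANCOVA sentence fixed in advance;
- standard errors that allow the variance to differ between arms, with a small-sample correction;
- the model fitted in each imputed data set and the arm contrasts pooled by a stated rule;
- adjusted mean differences with 95% confidence intervals as the reported result.

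Keep Kruskal–Wallis and Wilcoxon as a named sensitivity analysis.

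The Welch results above are the unadjusted counterpart of this model: coverage of about 95%, type I error of 4.9–5.6%, and verum–sham power of at least 99% under the planned figures. The adjusted model itself was not simulated.

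The cost is wording in section 2.9.1. It needs no extra patients, visits or data.
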